#### Safety during the exercise training sessions

While oxygen desaturation during exercise has been shown to be common in people with COPD, a recent study showed that oxygen desaturation below 80 % during a 6MWT only occurred in 26 out of 572 participants (i.e. 4.5 %) [16]. In the current study, it is anticipated that an even smaller proportion will desaturate below 80 % during exercise training as the intensity of exercise will be less than the peak achieved during the 6MWT. In addition, half the participants in this study will be allocated to the Oxygen Group and will receive oxygen during their exercise training sessions, thereby ameliorating any desaturation. For this reason, the decision has been made that the trainers will not monitor SpO_2_ during the training program. This will ensure that they stay blinded to group allocation. Nevertheless, to ensure participant safety, SpO_2_ will be monitored and recorded throughout the training program by a clinician who is not involved in exercise prescription or progression. A standardised pulse oximeter (RAD-5v Masimo Corp, Irvine, CA, USA) will be used at all sites. The pulse oximeter will be hidden from the participant and trainer in order to maintain blinding. This clinician will also be blinded to group allocation and will not reveal the changes in SpO_2_ to the trainer unless SpO_2_ falls below 80 % [17], at which point the participant will be asked to stop exercising and rest. The participant will be instructed to recommence exercising when SpO_2_ returns to 88 %. The clinician will monitor the initial exercise training session and, thereafter, will monitor an entire training session once a week for the remainder of the training program.

### Participant education

At the end of the exercise training program an education booklet [18] will be provided and an individualised home maintenance exercise program will be given to all participants. All participants will be encouraged to complete the home exercise program for six months after which they will return for reassessment. No supplemental oxygen will be provided for the home program.

### Outcome measures

The primary outcomes will be endurance exercise capacity measured by the endurance shuttle walk test (ESWT) [19] and HRQoL measured by the Chronic Respiratory Disease Questionnaire (CRQ) [20]. The secondary outcomes will be peak exercise capacity measured by the incremental shuttle walk test (ISWT) [21], level of dyspnoea using the Dyspnoea-12 Questionnaire [22] and physical activity levels measured by a multi-sensor activity monitor (SenseWear MF, BodyMedia, Pittsburgh USA) worn for seven days.

An assessor who is blinded to group allocation will carry out all outcome measures at baseline, at the completion of exercise training and six months following completion of the exercise training program. All the exercise outcome measures at each time point, will be performed with the participant breathing room air.

### Primary outcomes

Endurance exercise capacity: Endurance exercise capacity will be measured by the ESWT, performed according to a published protocols [19]. The ESWT is an externally paced constant work rate test which is performed at a walking speed equivalent to 85 % of the participant’s peak speed achieved on the incremental shuttle walk test (ISWT) [23]. Participants will be asked to walk for as long as possible, back and forth along a 10 metre shuttle course, in time to a pre-recorded auditory signal. Dyspnoea and RPE will be recorded each minute during the test and at the beginning and end of the test using the modified Borg 0–10 Scale [14, 15]. Heart rate and SpO_2_ will be monitored continuously using a portable saturation monitor (RAD-5v Masimo Corp, Irvine, CA, USA) and recorded each minute. At the end of the test, each participant will be asked to identify the main reason for stopping the test.

The ESWT will be performed twice at all assessment time points. Participants will rest for at least 30 minutes between tests or until SpO_2_, dyspnoea and heart rate have returned to resting levels. Due to the ceiling effect of 20 minutes in the ESWT [19], the ESWT protocol will be modified so that if the participant completes more than 10 minutes in the first baseline ESWT, the test will be stopped and repeated at a higher level. The goal is to have each participant's baseline ESWT time between five and 10 minutes. This will allow the test to demonstrate improvement without reaching the 20 minute test termination at assessments after training. The walking speed for repeat testing of the ESWT after exercise training and at six-month follow-up will remain the same as that of the participant’s highest level baseline test. The greater time walked in the ESWT at each assessment time point will be recorded for analysis. The minimal important difference for the ESWT following ground walking training in people with COPD is 156 seconds [24].

HRQoL: The interviewer-administered version of the CRQ [20] will be used to measure disease-specific HRQoL. The questionnaire consists of 20 questions which are grouped into one of four domains: dyspnoea (5 questions), fatigue (4 questions), emotional functioning (7 questions) and mastery (4 questions). Each question is scored from one to seven, with a higher score indicating a better health status. A total score, as well as individual domain scores, will be calculated. The CRQ has been shown to be a reliable and valid tool for measuring HRQoL in people with chronic respiratory disease [20]. A change of 0.5 in the mean score per domain (calculated by dividing the overall score by the number of questions) has been shown to be associated with a minimal important difference in health status [25]. This means that a minimal important difference would be 2.5 for dyspnoea, 2 for fatigue, 3.5 for emotional function, 2 for mastery, and 10 for the total CRQ score.

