### Sample size

A total of 110 participants (55 per group) will be recruited to ensure that 88 participants complete the study, allowing for a 20 % loss to follow-up. Regarding primary outcomes, 88 participants will be sufficient to provide 80 % power to detect as significant, at the (two-sided) 5 % level, a minimum 156 second difference [24] in the mean ESWT time between the Oxygen Group and the Air Group. This assumes a standard deviation of 250 seconds for the ESWT, as has been previously reported when comparing two modes of exercise training in COPD [31]. For the HRQoL outcome, 88 participants will be sufficient to provide 80 % power to detect as significant, at the (two-sided) 5 % level, a minimum 10 point difference [32] in the mean CRQ total score between the groups, assuming a standard deviation (SD) of 17 points [33].

Regarding secondary outcomes, 82 participants will be sufficient to provide 80 % power to detect as significant, at the (two-sided) 5 % level, a minimum of 2.5 point difference (a change of 0.5 point per question for a total of five questions in the dyspnoea domain) between groups in the mean score of the dyspnoea domain of the CRQ, assuming a SD of 4.0 [34]. For the physical activity outcome, 82 participants will be sufficient to provide 80 % power to detect as significant, at the (two-sided) 5 % level, a minimum of 1845 step difference in the mean steps per day between the groups, assuming a SD of 2968 steps for people with moderate to severe COPD [35].

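### As worded, the longer-time rule records the stopped, slower first walk as the ESWT baseline for a participant moved up a level whose repeat meets the 5 to 10 minute goal

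*Protocol article*

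**What the plan says.** All the relevant rules stand in the Primary outcomes section of the protocol article, in the paragraphs on endurance exercise capacity:

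- Number of tests: "The ESWT will be performed twice at all assessment time points".
- Moving up: "if the participant completes more than 10 minutes in the first baseline ESWT, the test will be stopped and repeated at a higher level".
- Target: "The goal is to have each participant's baseline ESWT time between five and 10 minutes".
- Speed at follow-up: it "will remain the same as that of the participant’s highest level baseline test".
- Value analysed: "The greater time walked in the ESWT at each assessment time point will be recorded for analysis".

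The follow-up rule carries a qualifier about level. The rule for the analysed value does not. The ESWT is one of two primary outcomes, and the Sample size section plans for "a minimum 156 second difference [24] in the mean ESWT time between the Oxygen Group and the Air Group", with a standard deviation of 250 s.

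**The concern.** Between two walks at the same speed, the longer is the better performance. Between walks at different speeds it need not be, and here the slower walk was ended by the assessor. Its duration shows only that the participant could pass 10 minutes at that speed.

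For a participant moved up a level, the baseline would be a near-constant value just above 600 s at one work rate, and the follow-up value an endurance time at a faster one. Three things are at stake: the within-group change that readers will compare with the 156 s minimal important difference, the usefulness of baseline as a covariate, and some precision. There is also a practical risk. Seven sites apply the rule, and some may follow the literal wording while others follow the presumed intent, which would mix two definitions of baseline.

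**Working it through.** **1. The plan's own figure.** Inputs from the Sample size section: difference 156 s, SD 250 s, two-sided 5 %, 80 % power, 88 completers, 20 % loss.

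- n per arm = 2 × (1.960 + 0.842)² × 250² / 156² = 40.3, rounded up to 41 (82 in total).
- With 44 per arm: 156 / (250 × √(2/44)) = 2.927; 2.927 − 1.960 = 0.967; power 83.3 %.
- 88 / (1 − 0.20) = 110.

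The planned 88 completers are sufficient for the ESWT.

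**2. The rules applied in order to one participant who is moved up.**

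- First test: passes 10 minutes and is stopped. Recorded time just over 600 s, slower level.
- Repeat: 300 to 600 s if the goal is met, faster level.
- Longer of the two: the stopped test, in every case where the goal is met.
- Follow-up: faster level.

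The rule picks the right test only if the repeat outlasts the stopped one, that is, if the goal is missed on the long side.

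**3. Size per affected participant.** Overstatement = 600 − T, where T is the time at the higher level.

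| T (s) | Overstatement (s) | As a multiple of 156 s |
|---|---|---|
| 300 | 300 | 1.92 |
| 450 | 150 | 0.96 |
| 600 | 0 | 0 |

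A participant with T = 450 s who gains exactly 156 s reaches 606 s, but the recorded change is about 6 s.

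**4. Size across the trial.** The share moved up, f, is not stated. Assumptions: f from 10 to 40 %; times at the follow-up level uniform over 300 to 600 s for everyone (mean 450, variance 300²/12 = 7500); moving up unrelated to that time; baseline to post-training correlation 0.50; post-training SD 250 s.

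- Mean shift = 150 × f.
- Variance of the recorded baseline = (1 − f) × (7500 + 22500 f), and its covariance with the post-training value is (1 − f) times the correct one. So the observed correlation is r = 0.50 × √[(1 − f)/(1 + 3f)].
- Covariate-adjusted SD = 250 × √(1 − r²). Power is computed as in step 1 with this SD and 44 per arm.

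| f | Mean shift (s) | Share of 156 s | r | Adjusted SD (s) | Power |
|---|---|---|---|---|---|
| 0 | 0 | 0 % | 0.50 | 217 | 92 % |
| 10 % | 15 | 10 % | 0.42 | 227 | 90 % |
| 20 % | 30 | 19 % | 0.35 | 234 | 88 % |
| 30 % | 45 | 29 % | 0.30 | 238 | 87 % |
| 40 % | 60 | 38 % | 0.26 | 241 | 86 % |

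**5. A more pessimistic variant.** Take 250 s as the SD of an unadjusted change score and let the baseline error add to it independently. Error variance = 30000 f − (150 f)². The SD becomes √(250² + error variance): 255, 260, 264 and 266 s for f = 10, 20, 30 and 40 %. Power with 88 falls from 83.3 % to 81.7, 80.4, 79.3 and 78.5 %; at f = 50 % it is 77.9 % (SD 268 s).

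**The case against.** The strongest reply is that the text allows a sensible reading. A test that is stopped and then repeated is naturally taken as replaced. A time above 10 minutes lies outside the stated target for the baseline, and follow-up is anchored to the highest level. On this reading the longer time is chosen only among valid tests at the working level. That is probably what was meant. But no sentence excludes the stopped test, and the qualifier about level is missing from the one rule that defines the analysed value.

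A second reply is that a journal article leaves such detail to the full protocol or the test manual. That would answer an omission. Here the article states the selection rule, and the rule conflicts with the sentences beside it.

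A third reply stands. The Randomisation section places the baseline assessments before allocation, the rule is the same in both arms, and allocation is stratified by site. Any shift is therefore equal in expectation and cancels from the difference between groups, which is the comparison the trial is powered for. A reader might infer a biased treatment effect; the document does not support that.

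A reader might also infer that every participant moved up is affected. That is too wide, because a repeat that outlasts the stopped test is selected correctly.

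**Conclusion.** The wording is wrong as it stands and should be corrected. For a moved-up participant whose repeat meets the 5 to 10 minute goal, it records the truncated, slower walk as baseline while follow-up is at the faster speed. The overstatement of 0 to 300 s per affected participant follows from the protocol's own limits. The trial-level shift of 15 to 60 s and the fall in correlation from 0.50 to between 0.42 and 0.26 rest on an assumed share moved up, an assumed uniform distribution and an assumed correlation, none of which the document gives.

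The harm is to within-group change, to its comparison with 156 s, to the baseline covariate and to precision. It is not a systematic between-group bias. Nor does it show that the trial is underpowered: with covariate adjustment, power stays at 86 % or more over the assumed range, and only the pessimistic variant dips slightly below 80 %, from about 30 % moved up.

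A reader might add that a chance imbalance in the number moved up would set off the switch to ANCOVA in the Data analysis section. That section gives no threshold for a baseline difference, and the conditional choice of model is a separate matter that adds no weight here.

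**What to change.** Replace the sentence on the analysed value with wording to this effect: for the baseline ESWT, analyse the longest walk among those done at the participant's highest level, which is the level kept for all later assessments; do not use a lower-level walk that was stopped at 10 minutes; after training and at six months, analyse the longer of the two walks.

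Repeat this as an instruction on the case report form so that all seven sites record the same quantity. The wording works whether one or more tests are done at the highest level. The cost is one protocol sentence and one form instruction, with no extra test and no change to the planned 110 participants.

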### Secondary outcomes

Peak exercise capacity will be measured using the ISWT which is an incremental, externally paced, symptom-limited test with walking speed increasing each minute [26]. The participant will be asked to walk back and forth along the 10 metre shuttle course in time with the pre-recorded auditory signals. There are 12 one-minute levels, with each level requiring the participant to perform successively more shuttles in each minute. Dyspnoea and RPE will be recorded at the beginning and end of the test and each minute during the test using the modified Borg 0–10 Scale [14, 15]. Heart rate and SpO_2_ will be monitored continuously using a portable saturation monitor (RAD-5v Masimo Corp, Irvine, CA, USA) and recorded each minute. The test is terminated when the participant chooses to stop or when, on two consecutive auditory signals, the participant is more than one metre from the closest cone [26]. At the end of the test, participants will be asked to identify the main reason for stopping.

The ISWT will be performed twice at baseline and at subsequent assessments to account for a learning effect [26] and the greater distance recorded for analysis. Participants will rest for at least 30 minutes between tests or until SpO_2_, dyspnoea and heart rate have returned to resting levels. The minimal important difference for the ISWT for pulmonary rehabilitation is 47.5 metres (95 % confidence intervals 38.6 to 56.5 metres) [27].

Dyspnoea will be measured by the Dyspnoea-12 questionnaire [22]. The Dyspnoea-12 questionnaire consists of 12 descriptor items on a scale of none (zero point), mild (one point), moderate (two points), or severe (three points). It provides an overall score for severity of dyspnoea that incorporates seven items pertaining to the quality of the sensation of dyspnoea and five items pertaining to the emotional response to the sensation of dyspnoea. The time reference period for “these days” captures the current level of dyspnoea experienced by the participants as opposed to specifically on the day of the test or in response to a specific activity. The total score for the Dyspnoea-12 questionnaire ranges from 0 to 36, with higher scores corresponding to greater severity of dyspnoea.

Physical activity will be measured by a multi-sensor activity monitor (SenseWear MF, BodyMedia, Pittsburgh, USA). This device provides information on activity intensity via energy expenditure, duration of levels of energy expenditure and step count. The activity monitor will be worn continuously over a seven-day period at baseline, at the completion of exercise training and at the six-month follow-up assessment. Minimum wear time will be set at three days for at least 20 hours per day. This device is well tolerated in people with COPD [28] and has been shown to provide a reliable and valid measure of physical activity in people with COPD [29, 30].

### Additional measures

At each assessment time point, spirometry (EasyOne handheld Spirometer, ndd Medical Technologies, Chelmsford, MA) will be performed to determine whether the participant’s lung function remains stable during the study period.

### Data analysis

For all outcome measures the primary analyses will be via intention-to-treat and will be conducted by a statistician who has not been involved in the study and is unaware of group allocation. Data will be analysed using linear mixed models or analysis of covariance (ANCOVA) if there are between group differences at baseline. Uncertainty regarding the size of the mean between group differences will be quantified with 95 % confidence intervals.

### Sample size

A total of 110 participants (55 per group) will be recruited to ensure that 88 participants complete the study, allowing for a 20 % loss to follow-up. Regarding primary outcomes, 88 participants will be sufficient to provide 80 % power to detect as significant, at the (two-sided) 5 % level, a minimum 156 second difference [24] in the mean ESWT time between the Oxygen Group and the Air Group. This assumes a standard deviation of 250 seconds for the ESWT, as has been previously reported when comparing two modes of exercise training in COPD [31]. For the HRQoL outcome, 88 participants will be sufficient to provide 80 % power to detect as significant, at the (two-sided) 5 % level, a minimum 10 point difference [32] in the mean CRQ total score between the groups, assuming a standard deviation (SD) of 17 points [33].

Regarding secondary outcomes, 82 participants will be sufficient to provide 80 % power to detect as significant, at the (two-sided) 5 % level, a minimum of 2.5 point difference (a change of 0.5 point per question for a total of five questions in the dyspnoea domain) between groups in the mean score of the dyspnoea domain of the CRQ, assuming a SD of 4.0 [34]. For the physical activity outcome, 82 participants will be sufficient to provide 80 % power to detect as significant, at the (two-sided) 5 % level, a minimum of 1845 step difference in the mean steps per day between the groups, assuming a SD of 2968 steps for people with moderate to severe COPD [35].

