### Randomisation

Participants who meet the study inclusion criteria and complete the baseline assessments will be randomly allocated into one of the two groups: Oxygen Group or Air Group. Equal numbers of participants will be randomised to each group. Sequence generation will be determined using a computerised random number generator with stratification for study site, six-minute walk distance (6WMD) (≤350 metres vs >350 metres) and level of nadir SpO_2_ from the 6MWT (nadir SpO_2_ between 89-86 % vs < 86 %). Allocation concealment will be achieved by the use of a central telephone randomisation system coordinated through the National Health and Medical Research Council Clinical Trials Centre at The University of Sydney. This will ensure that the researchers are blinded to the sequence generation.

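### On the printed inputs, 88 completers give about 79% power for the CRQ total score (78% by t-test), slightly below the stated 80%

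*Protocol article*

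**What the plan says.** The Sample size section gives a separate calculation for each of the two primary outcomes, the endurance shuttle walk test (ESWT) and the CRQ total score. The effect assumed for the second is "a minimum 10 point difference [32] in the mean CRQ total score between the groups, assuming a standard deviation (SD) of 17 points". The claim made for that effect, with a two-sided test at 5%, reads: "For the HRQoL outcome, 88 participants will be sufficient to provide 80 % power".

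The recruitment target follows from the 88: "A total of 110 participants (55 per group) will be recruited to ensure that 88 participants complete the study", with 20% loss to follow-up. The Randomisation section fixes the ratio: "Equal numbers of participants will be randomised to each group".

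The CRQ calculation mentions no baseline correlation or other reduction in variance. The Data analysis section names linear mixed models, or ANCOVA if the groups differ at baseline.

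**The concern.** Every input needed to check the CRQ claim is printed, and the result does not follow from them. The standardised difference for CRQ total (10/17 = 0.588) is the smallest of the four in the section, so it needs the most participants. Yet it is assigned the same 88 as the ESWT, whose standardised difference is 0.624.

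What is at stake is the accuracy of a stated operating characteristic for a primary outcome. The type II error implied by the printed assumptions is 21% to 22%, where the text implies 20%. Anyone citing the planned power beside a null CRQ result would be citing a slightly favourable figure.

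**Working it through.** **Inputs.** From the Sample size section: difference 10 points, SD 17, two-sided 5%, 80% power, 88 completers, 20% loss. From the Randomisation section: 1:1 allocation, hence 44 per group.

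**Step 1: find the formula that reproduces the section's other figures.** Normal approximation, n per group = 2 × (1.960 + 0.842)² × (SD/difference)².

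| Outcome | Difference / SD | n per group, unrounded | Total | Stated total |
|---|---|---|---|---|
| CRQ dyspnoea domain | 2.5 / 4.0 | 40.2 | 82 | 82 |
| Steps per day | 1845 / 2968 | 40.6 | 82 | 82 |
| ESWT | 156 / 250 | 40.3 | 82 | 88 (ample) |
| CRQ total | 10 / 17 | 45.4 | 92 | 88 (short) |

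The two 82s come back exactly. By the t-test (noncentral t) both would need 84, and 82 gives 79.8% and 79.4% power. The normal formula is therefore the like-for-like comparison. For the ESWT, 88 gives 83.3% power (82.5% by t-test).

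**Step 2: power for CRQ total at 44 per group.**
- Standard error of the difference: 17 × √(2/44) = 3.62.
- Ratio: 10/3.62 = 2.76.
- Normal formula: Φ(2.76 − 1.96) = 78.8%.
- Noncentral t, 86 degrees of freedom: 77.9%.

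**Step 3: completers needed for 80%.**
- Normal formula: 45.4, rounded up to 46 per group, 92 in total. Even the unrounded total, 90.7, exceeds 88.
- t-test: 47 per group, 94 in total.
- A one-sided test would need 72, so sidedness does not explain 88.

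**Step 4: loss to follow-up.** 88/0.8 = 110, as stated; this step is right. For comparison, 92/0.8 = 115 and 94/0.8 = 117.5, so 118.

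**Step 5: what 88 completers do support at 80% power.**
- Keeping SD 17: a difference of (1.960 + 0.842) × 3.62 = 10.2 points (normal), or 10.3 (t-test).
- Keeping 10 points: an SD of 10 / [2.802 × √(2/44)] = 16.7 (normal), or about 16.6 (t-test).

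**Step 6: sensitivity to rounding of the SD.** An SD printed as 17 could lie anywhere from 16.5 to just under 17.5. Power at 88 by the normal formula runs from 81.1% (SD 16.5) to 76.5% (SD 17.49); by t-test, from 80.3% to 75.5%.

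**The case against.** The strongest reply is that the gap is within the precision of the inputs. The SD is printed to the nearest whole point. Any value from 16.5 to about 16.7 would print as 17 and give at least 80% at 88 by the normal formula. Since neither the ESWT nor the secondary outcomes yields 88, the CRQ calculation with an unrounded SD may be where 88 came from. This stands as a possible explanation; the documents neither confirm nor exclude it. It does not make the printed sentence correct, because a reader can only use 17.

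A second reply is that a baseline-adjusted analysis would recover the power. If 17 is the SD of follow-up scores, an assumed baseline correlation of 0.2 gives 80.4% (normal) or 79.5% (t-test), and 0.3 gives 82.4% or 81.6%. But the section states no correlation, does not say whether 17 is the SD of follow-up scores or of change, and the Data analysis section makes ANCOVA conditional. If 17 is an SD of change, these figures do not apply.

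A third reply is that the planned 95% confidence intervals, not the planned power, will carry the interpretation of a null result. That is fair and limits the consequence.

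Two stronger readings should be resisted. A reader might infer that the CRQ was overlooked when the trial was sized; the documents do not say which outcome set 88. A reader might also infer that the trial is materially underpowered for quality of life; a gap of 1 to 2 points, smaller than the effect of rounding the SD, does not support that.

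**Conclusion.** The point holds as a minor error in a stated figure for one of the two primary outcomes. With a difference of exactly 10, an SD of exactly 17, two-sided 5% and 44 per group, power is 78.8% by the formula that reproduces the section's 82s, and 77.9% by t-test. Reaching 80% takes 92 completers (4 more) or 94 (6 more). This rests on an unadjusted two-group comparison of means, the only calculation the printed inputs allow. The cause is not established; a rounded SD is possible. The loss-to-follow-up step and the two secondary calculations need no correction, and 88 is ample for the ESWT.

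**What to change.** Amend the CRQ sentence in the Sample size section in one of these ways:

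- State that 88 completers give about 79% power (78% by t-test) for a 10-point difference with SD 17.
- State that 88 completers give 80% power for a difference of about 10.2 points (normal formula) or 10.3 points (t-test) with SD 17.
- Keep 80% and 10 points, and print the unrounded SD or the baseline correlation that justifies 88.

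If power is quoted from a baseline-adjusted model, give the assumed correlation with it and state that 17 is the SD of follow-up scores. Naming the formula used would let a reader reproduce all four figures.

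The cost is one sentence and, in the first two versions, a slightly less favourable claim. The target of 110 and the design can stay as they are.
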